### Statistical considerations

We aim to compare the effects of three different antithrombotic treatment strategies on endogenous fibrinolysis. The study will seek to evaluate the extent to which Very Low Dose Rivaroxaban (Group 2) reduces LT compared to Group 1 and Group 3. Separate paired comparisons will be used to evaluate univariate effects between the study groups at 2 weeks, 4 weeks and 8 weeks. Similarly, the influence of Very Low Dose Rivaroxaban will be evaluated by considering change over time from baseline using paired comparisons. Multivariable models (mixed models) will be used to estimate adjusted difference for baseline patient characteristics, and to evaluate the influence of secondary variables on the treatment outcome. The effect of treatment group on major adverse cardiac events may be considered using Kaplan–Meyer, or Cox regression should sufficient events be determined to achieve reasonable power. Time to event is defined as the time from randomisation to the date of event and the censor date is defined as the last follow-up date for each participant i.e. 6 months from date of randomisation.

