### Randomisation and study groups

Allocation of patients to one of the three study groups will be made by the use of a web-based block randomisation process. In subjects whose screening blood test shows that fibrinolytic status is impaired (LT > 2000 s), full written informed consent will be obtained, and patients will be randomised to one of 3 treatment arms in a 1:1:1 ratio: clopidogrel 75 mg daily (Group 1); clopidogrel 75 mg daily plus rivaroxaban 2.5 mg twice daily (Group 2); ticagrelor 90 mg twice daily (Group 3), in addition to standard therapy with aspirin 75 mg daily. For patients randomised to a new drug, for example patients initially treated with ticagrelor who are subsequently randomised to clopidogrel, a loading dose of the new medication will be given (clopidogrel 300 mg or ticagrelor 180 mg). The duration of rivaroxaban is 30 days after which the patient will stop rivaroxaban and will continue clopidogrel only or be switched to ticagrelor (including with loading), as decided by the clinical care team. Duration of P2Y_12_ inhibitor treatment will be determined by the clinical care team. All other treatments will be continued in accordance with standard of care, at the discretion of the clinical team.

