### Primary and secondary endpoints

The primary outcome measure is the change in fibrinolytic status as measured by Lysis Time (LT) using the GTT from admission to follow-up at 4 weeks post-discharge.

The secondary outcome measures are clinical events including re-intervention (further coronary angioplasty), major adverse cardiac events (composite of heart attack, stroke or death) and bleeding events evaluated by BARC criteria [23].

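### Between-arm lysis-time comparisons are called paired although the arms are independent, and as written they are unadjusted for admission lysis time

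*Protocol article*

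**What the plan says.** Under Randomisation and study groups, the protocol article uses a "web-based block randomisation process" and states that "patients will be randomised to one of 3 treatment arms in a 1:1:1 ratio". It describes no matching and no crossover. Entry requires a screening LT above 2000 s.

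Under Primary and secondary endpoints, the primary outcome is the "change in fibrinolytic status as measured by Lysis Time (LT) using the GTT from admission to follow-up at 4 weeks" after discharge.

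Under Statistical considerations, the aim is to evaluate "the extent to which Very Low Dose Rivaroxaban (Group 2) reduces LT compared to Group 1 and Group 3". Three analyses of LT follow, and none is ranked above the others:

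- Between arms: "Separate paired comparisons will be used to evaluate univariate effects between the study groups at 2 weeks, 4 weeks and 8 weeks".
- Over time: the influence of rivaroxaban is evaluated by "considering change over time from baseline using paired comparisons".
- Adjusted: "Multivariable models (mixed models) will be used to estimate adjusted difference for baseline patient characteristics". Admission LT is not named among those characteristics.

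**The concern.** A paired test needs a natural link between two observations. Two visits of the same patient have one; two patients in separately randomised arms do not. Taken literally, the result between arms would depend on how the records happen to be sorted, and patients would have to be dropped whenever the arms differ in size. With 10% loss planned, unequal arms are likely.

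The next sentence of the same section uses the same word for within-patient change, where it is correct. An analyst working from the text cannot tell that the meaning shifts between the two sentences.

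Reading the word as *pairwise* removes the impossible test but not the whole problem. The between-arm tests are still described as univariate, so chance imbalance in admission LT passes into them. The change-over-time analysis, as worded, is within patients. In a population selected for high LT it would show a fall without any drug effect. The comparison that answers the trial's question is the difference between arms at 4 weeks, allowing for admission LT, and neither of these two analyses supplies it.

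**Working it through.** **The plan's own figure.** The Sample size calculation section gives 45 per group and no SD, so the 45 cannot be reproduced. The inflation for loss can: 45/0.9 = 50 per group, and 3 × 50 = 150.

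**What literal pairing would cost.** For 80% power to detect 90 s with 45 per arm in a two-sample test, the implied SD is 90 / [(1.960 + 0.842) × √(2/45)] = 152.4 s. Two independent arms of 45 with that SD were simulated 40,000 times and paired arbitrarily:

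| Test | Type I error | Power for 90 s |
|---|---|---|
| Paired, arbitrary pairs | 5.1% | 78.0% |
| Two-sample | 5.1% | 78.9% |

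With equal arms the loss is about one point of power. With unequal arms the paired test is not defined unless patients are discarded.

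**An LT distribution for illustration.** The article gives no SD, so these inputs are assumptions:

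- 14% with LT ≥ 2500 s (Background, STEMI study): normal quantile 1.080.
- 25 of 65 screened patients randomised (Status quo), treated as the share with LT > 2000 s: 0.385, normal quantile 0.293.
- LT normally distributed, with the same SD at admission and at 4 weeks before selection. The screening LT is taken as the admission LT.

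SD = (2500 − 2000)/(1.080 − 0.293) ≈ 635 s, and mean = 2000 − 0.293 × 635 ≈ 1814 s.

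Among patients above 2000 s, the ratio of normal density to tail area is 0.994. The variance is therefore multiplied by 1 + 0.293 × 0.994 − 0.994² ≈ 0.304, which gives an SD of about 351 s. The mean becomes 1814 + 0.994 × 635 ≈ 2445 s.

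**Variance with and without admission LT.** For an assumed retest correlation r:

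- adjusted: 635²(1 − r²)
- 4-week LT, unadjusted: 635²(1 − r²) + r² × 351²
- change score, unadjusted: 635²(1 − r²) + (1 − r)² × 351²

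| r | Adjusted / 4-week LT | Reduction | Adjusted / change | Reduction |
|---|---|---|---|---|
| 0.5 | 0.908 | 9% | 0.908 | 9% |
| 0.7 | 0.774 | 23% | 0.949 | 5% |
| 0.9 | 0.435 | 56% | 0.984 | 2% |

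For r = 0.5: 635² × 0.75 = 302,419 and 0.25 × 351² = 30,800, so 302,419/333,219 = 0.908. The SD cancels from these ratios. They depend only on r, normality and the share of patients above 2000 s.

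**Chance imbalance.** The difference in mean admission LT between two arms of 45 has SD 351 × √(2/45) ≈ 74 s. Multiplying by r, about 37, 52 or 67 s of this carries into an unadjusted 4-week comparison at r = 0.5, 0.7 or 0.9. The sample size section mentions differences of 90 s and 45 s.

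**Regression to the mean.** Without any treatment effect, the expected fall in every arm is (1 − r) × (2445 − 1814) = (1 − r) × 631, or about 316, 189 or 63 s at r = 0.5, 0.7 or 0.9. On these assumptions, even the smallest is larger than 45 s.

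**The case against.** The strongest reply is that *paired* is a slip for *pairwise*. The preceding sentence sets Group 2 against Groups 1 and 3, and separate comparisons between groups fit that reading. It is the likelier meaning. It cannot be taken as certain, because the following sentence uses the word in its proper sense, and it still leaves an unadjusted between-arm test.

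A reader might infer that admission LT goes unused. The article does not support that. Admission LT is half of the primary change outcome, it enters the change-over-time analysis, and the mixed models may include it among baseline characteristics. What stands is narrower: the stated between-group tests are univariate, and no adjusted 4-week contrast is put forward as the primary analysis.

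It can also be said that model detail belongs in an analysis plan that is not shown. That is right for further covariates and the covariance structure, and their absence is no fault here. It does not excuse a test that is stated and does not fit the design.

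The objections to the figures are fair as well. The larger reductions are against raw 4-week LT, which is not the stated outcome; against change scores the gain is small. The SD of 635 s is rough: the 14% comes from STEMI patients only, 25/65 also reflects consent and eligibility, and using the Background's NSTEMI figure (23% at LT ≥ 3000 s) gives about 2,240 s. The variance ratios survive that change of SD. The amounts in seconds do not.

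**Conclusion.** The wording is wrong for the design: nothing pairs patients across the three arms, and a paired test fails when evaluable numbers differ. On the pairwise reading, the between-group tests are still unadjusted for admission LT, and within-arm change cannot stand in for them because patients are selected on high LT.

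The gain from adjustment is about 2–9% of variance against unadjusted change scores and about 9–56% against unadjusted 4-week LT. It rests on assumed retest correlations of 0.5 to 0.9, normality, and the rough selected share of 25/65.

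It would go too far to call the primary comparison invalid on error control. In equal arms, arbitrary pairing leaves the type I error near 5% and costs about one point of power. Nor does regression to the mean bias a randomised between-arm contrast; it undermines only conclusions drawn from change within an arm. This is a correction that should be made, at modest numerical stake.

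**What to change.** In Statistical considerations:

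1. For comparisons between study groups, replace *paired* with *pairwise independent-sample*. Keep *paired* for within-patient change.
2. Make the primary analysis the between-arm contrasts at 4 weeks, Group 2 against Group 1 and Group 2 against Group 3, from an ANCOVA or from the mixed model already planned, with admission LT as a covariate.
3. Keep the unadjusted between-arm results and the within-arm paired changes as supportive. State that the latter do not by themselves show a treatment effect.

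Further covariates and the covariance structure can be left to the statistical analysis plan. The cost is a change of wording: admission LT and all visits are already collected, and a mixed model is already planned.

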
A two-stage consent process is adopted where an eligible patient will first consent to a screening blood test to identify impaired endogenous fibrinolysis before proceeding to a full consent to allow for randomisation and trial procedures. In cases of patients presenting acutely to the hospital with STEMI for PPCI, a delayed consent approach is undertaken, with ethical permission, whereby screening blood tests for assessment of thrombotic status are taken at the same time as standard of care blood samples on arrival, and patients are consented for the study after the PPCI procedure when they are stable and able to carefully consider the study. This is to ensure the consent process is fully informed (patients presenting with STEMI are unwell and often haemodynamically unstable, thus may not be in a suitable state to give full informed consent) and does not impact on the clinical care (explaining the study and obtaining full consent might cause delay to the emergency PPCI procedure) whilst not compromising the integrity of the sampling process (drugs such as heparin given during the procedure may affect the thrombotic status of patients). If after the emergency procedure the patient declines to participate or is unable to consent, the patient will not be included in the study. This will be recorded as a screen-fail. However, if the patient consents after the procedure, clinical information will be double checked to determine eligibility. If the thrombotic status is impaired and he/she fits the study criteria, written full informed consent will be obtained.

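### Beside its between-group analyses, the plan also offers paired change from baseline as evidence on rivaroxaban; read within arm, that test is confounded by regression to the mean, and no analysis is ranked as primary.

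*Protocol article*

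**What the plan says.** All references are to the protocol article.

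- **Entry (Randomisation and study groups).** Randomisation is confined to "subjects whose screening blood test shows that fibrinolytic status is impaired", defined as LT above 2000 s.
- **Timing of the screening sample (Inclusion and exclusion criteria).** For STEMI, "screening blood tests for assessment of thrombotic status are taken at the same time as standard of care blood samples on arrival". The text describes no second LT measurement before treatment.
- **Primary outcome (Primary and secondary endpoints).** The definition reads: "The primary outcome measure is the change in fibrinolytic status as measured by Lysis Time (LT) using the GTT from admission to follow-up". The visit in question is the one at 4 weeks.
- **Analysis (Statistical considerations).** Four statements stand side by side:
  1. The aim is to evaluate "the extent to which Very Low Dose Rivaroxaban (Group 2) reduces LT compared to Group 1 and Group 3".
  2. "Separate paired comparisons will be used to evaluate univariate effects between the study groups at 2 weeks, 4 weeks and 8 weeks".
  3. Similarly, "the influence of Very Low Dose Rivaroxaban will be evaluated by considering change over time from baseline using paired comparisons".
  4. "Multivariable models (mixed models) will be used to estimate adjusted difference for baseline patient characteristics".

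None of the four is named as the primary analysis of the primary outcome.

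**The concern.** Statement 3 is naturally read as a before-and-after test within the rivaroxaban arm, offered as evidence about the drug. The baseline of that test is a value on which patients were selected. When patients enter because one measurement was high, their mean falls at the next measurement with no treatment effect, to an extent set by how imperfectly the two measurements correlate. A paired test against zero cannot separate this fall from a drug effect.

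The placement makes it matter. The primary outcome is a change from admission, and statement 3 is the only one of the four that mentions change from baseline; the between-group sentence speaks of effects at visits. The Sample size calculation section also expresses its target partly as a change of 45 s. With no ranking, an analyst could follow the text faithfully and report the paired p-value in Group 2 as a main finding. The conclusion at risk is the central one: that rivaroxaban improves fibrinolysis.

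**Working it through.** **Inputs from the document**
- Selection threshold: LT above 2000 s (Randomisation and study groups).
- 45 evaluable patients per group, two-sided alpha 0.05, power 0.80, targets of 90 s and 45 s (Sample size calculation).
- 25 of 65 screened patients randomised, 25/65 = 38% (Status quo).
- 14% of STEMI patients with LT of 2500 s or more in an earlier study (Background).

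**Assumptions, not in the document**
- LT is normal with the same mean and SD at both times.
- 38% stands in for the share above 2000 s.
- The screening value is the baseline.
- The retest correlation r lies between 0.5 and 0.95.

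**Step 1: the plan's own figure.** The dropout step reproduces: 45/0.9 = 50, and 3 × 50 = 150. The 45 cannot be checked because no SD is given. Solving backwards with z values summing to 2.80, a two-sample comparison of 90 s implies SD = 90/(2.80 × √(2/45)) ≈ 152 s.

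**Step 2: two anchors for the SD.**
- *Wide.* The normal quantiles for upper tails of 38% and 14% are 0.293 and 1.080. SD = (2500 − 2000)/(1.080 − 0.293) ≈ 635 s; mean = 2000 − 0.293 × 635 ≈ 1814 s.
- *Narrow.* SD 152 s from step 1, with the same 38% above 2000 s.

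**Step 3: expected fall with no drug effect.**
Fall = (1 − r) × SD × φ(k)/(1 − Φ(k)), where k = (2000 − mean)/SD = 0.293 and the ratio is 0.994. At SD 635 s the enrolled mean is 1814 + 0.994 × 635 ≈ 2445 s, so at r = 0.5 the fall is 0.5 × 631 ≈ 316 s.

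**Step 4: how often the within-arm paired test is significant.**
Var(change) = (1 − r)² × (SD among those enrolled)² + SD² × (1 − r²). At SD 635 s the SD among those enrolled is about 351 s. At r = 0.5 the variance is 0.25 × 351² + 635² × 0.75, giving an SD of change of about 577 s and a non-centrality of 316 × √45/577 ≈ 3.67. The non-central t with 44 degrees of freedom then gives 95%.

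| r | Fall, SD 635 s | Fall, SD 152 s | Within-arm test significant |
|---|---|---|---|
| 0.5 | 316 s | 76 s | 95% |
| 0.7 | 189 s | 45 s | 76% |
| 0.8 | 126 s | 30 s | 57% |
| 0.9 | 63 s | 15 s | 32% |
| 0.95 | 32 s | 8 s | 18% |

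The last column does not depend on the SD, because fall and SD of change scale together. It depends on r, n and the share above the threshold.

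**Step 5: between-arm comparison.** In 2000 simulated null trials per setting, a two-sample t-test on change between two arms was significant in about 4.4% to 5.9%, whatever r or SD. The common fall cancels.

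**Step 6: sensitivity to the share above 2000 s.** With 50% instead of 38%, the within-arm rates are 81%, 57% and 22% at r = 0.5, 0.7 and 0.9.

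**The case against.** The strongest reply is that the valid analysis is already in the plan. The section opens with a comparison of Group 2 against Groups 1 and 3, adds between-group comparisons at each visit and mixed models, and the Hypothesis section is comparative too. A reader might infer that rivaroxaban will be judged by within-arm change alone, or that a fall significant in Group 2 but not in the other arms would count as success. The text supports neither: it contains no such decision rule, and the within-arm test is one analysis among several. This part of the objection stands and limits the point.

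Second, *paired* may mean *pairwise*. The preceding sentence uses the word for comparisons between independent arms, and the sentence at issue begins with *Similarly*. It could therefore mean between-arm comparisons of change, which regression to the mean does not bias. That reading is possible, but the within-patient reading is at least as natural, and the wording needs correcting under either.

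Third, the article implies but does not state that the screening value is the baseline, and the visit flow is in a figure not available here. A separate later baseline would shrink the artefact.

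Fourth, a reader might add that recovery from the acute phase will pass for a drug effect. The documents report no such recovery of LT; the section on pharmacological modulation says only that fibrinolysis appears unaffected by dual antiplatelet therapy. It is a possible further contributor, no more.

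Fifth, the calibration is rough. The 25/65 ratio counts refusals as screening failures and so probably understates the share above 2000 s, and the 14% is from STEMI patients only. The seconds are therefore illustrative. The within-arm rates do not depend on the SD, and they stay well above 5% when the share is raised to 50%.

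**Conclusion.** The point holds in a limited form. The plan lists, with no lower rank than its between-group analyses, a paired change-from-baseline evaluation of rivaroxaban. If run within the arm, that evaluation is not valid evidence of a drug effect, because entry requires a high value of what appears to be the same baseline. With no drug effect and 45 patients, it would be significant in about 95% of trials at a retest correlation of 0.5 and 18% at 0.95, against a nominal 5%. The spurious fall would reach or pass the 45 s target at correlations up to at least 0.9 if the SD is 635 s, and up to about 0.7 if it is 152 s. These sizes rest on normality, the 38% proxy, the assumed range of correlation and the screening value serving as baseline.

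The documents do not show that the trial's conclusion will rest on this test. The defect is that nothing ranks the valid comparison above it.

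**What to change.** Reword the sentence in Statistical considerations so that:

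1. The effect of rivaroxaban is judged by the randomised between-group difference in LT at 4 weeks, Group 2 versus Group 1 and, as the plan already intends, versus Group 3, adjusted for admission LT. Name this as the primary analysis of the primary outcome.
2. *Paired* becomes *pairwise* wherever independent arms are compared.
3. Within-arm changes are reported descriptively, with a note that they include regression to the mean and are not evidence of a drug effect.
4. The text states whether the screening LT is the admission baseline.

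Cost: a few sentences in the protocol or analysis plan, with no new data and no extra patients. The within-arm change loses its p-value.

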### Sample size calculation

Sample size was calculated using Stata version 15.1 (StatCorp, College Station, TX, USA). Assuming α = 0.05 for two sided tests, to detect a difference of LT = 90 s with a power 1 – β = 0.80, a sample size of 45 in each group would be required to detect a change in LT = 45 s. Accounting for a 10% drop-out, withdrawal and loss to follow up, we calculated 50 patients in each group, resulting in a sample size of 150.

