Whilst treatment with DAPT addresses the enhanced platelet reactivity in ACS, ongoing activation of the coagulation cascade and impaired endogenous fibrinolysis are unaffected by current DAPT. There is increasing evidence that impaired endogenous fibrinolysis is a strong predictor of residual cardiovascular risk in patients with ACS. Altered fibrin clot structure and increased resistance of the clot to lysis have been associate with myocardial infarction and stent thrombosis [11–14]. In the last 2 years, two large prospective studies have confirmed that impaired fibrinolysis in patients with ACS is a novel independent marker of increased cardiovascular risk [15, 16]. In a sub-study of > 4000 patients in the PLATO trial, assessment of fibrin clot lysis using a validated turbidimetric assay revealed that impaired fibrin clot lysis was an independent predictor of adverse outcome in ACS [15]. After adjusting for established cardiovascular risk factors, each 50% increase in lysis time was associated with cardiovascular death/spontaneous MI [Hazard ratio [HR] 1.17, 95% confidence interval (CI) 1.05–1.31; p < 0.01] and cardiovascular death alone [HR 1.36, 95% CI 1.17–1.59; p < 0.001]. Earlier work employing a point-of-care assay of whole blood fibrinolysis showed that some 23% of patients with non ST-segment elevation myocardial infarction (NSTEMI) exhibit impaired endogenous fibrinolysis (lysis time, LT ≥ 3000 s) despite DAPT, and this is predictive of recurrent adverse cardiovascular events [HR: 2.52, p < 0.04] and cardiovascular death [HR: 4.2, p = 0.033] over the subsequent year. with hazard increasing with increasing lysis time [17]. More recently, the RISK PPCI study from our group, involving nearly 500 patients with ST-segment elevation myocardial infarction (STEMI) showed that impaired endogenous fibrinolysis (LT ≥ 2500 s) detected in 14% patients on admission was strongly related to recurrent major cardiovascular events (HR 9.1, 95% CI 4.28–15.03, p = 0.001), driven by cardiovascular death and myocardial infarction [16].

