## Status quo

The first patient in VaLiDate-R was enrolled in January 2019. As per April 2019, a total of 65 patients were screened and 25 patients were randomised. Recruitment is currently ongoing with the aim of randomising the last patient by the February 2020 and completing the study with 6-month follow up of the last patient by August 2020 and subsequent data lock.

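### The sample size statement ties two target values (90 s and 45 s) to the same 45 per group and 80% power, and under one test both cannot be right

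*Protocol article*

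**What the plan says.** The Sample size calculation section of the protocol article gives its assumptions in one sentence, plus a dropout step:

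- Error rate: "Assuming α = 0.05 for two sided tests".
- First target and power: "to detect a difference of LT = 90 s with a power 1 – β = 0.80".
- Sample size and second target, later in the same sentence: "a sample size of 45 in each group would be required to detect a change in LT" of 45 s.
- Dropout: "Accounting for a 10% drop-out, withdrawal and loss to follow up, we calculated 50 patients in each group", which makes 150 in all.

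The article prints no SD for LT or for change in LT.

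Two other sections bear on which comparison is meant. Primary and secondary endpoints defines the primary outcome as the change in LT from admission to 4 weeks. Statistical considerations says that Group 2 is to be compared with Group 1 and with Group 3, and also plans paired comparisons of change from baseline. Neither section links 90 s or 45 s to one of these analyses.

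**The concern.** One alpha, one power and one sample size are attached to two target values, one twice the other. For any single test with these fixed, the detectable difference is a constant multiple of the SD. Two targets in the ratio 2:1 therefore need two SDs in the ratio 2:1. No single SD, stated here or in a fuller document, can satisfy both.

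This is the only justification given for the trial's size, and it concerns the primary endpoint. If Group 2 shows no clear benefit, a reader cannot tell whether the trial was planned to detect 90 s or 45 s. On one of the two readings, the power for the smaller value is far below 80%.

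**Working it through.** **Inputs from the article.** Two-sided alpha 0.05, power 0.80, 45 per group, targets 90 s and 45 s, dropout 10%.

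**1. What reproduces.** 45 / (1 − 0.10) = 50 per group, and 3 × 50 = 150. The dropout step is correct. The 45 itself cannot be reproduced, because no SD is printed and two targets are named.

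**2. Implied SD for a two-sample t test.** With 45 per group (88 degrees of freedom) and 80% power, the noncentral t distribution gives a standardised difference of d = 0.597. SD = target / d.

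- 90 / 0.597 = 150.7 s
- 45 / 0.597 = 75.4 s

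The normal approximation, n = 2(1.960 + 0.842)² × (SD/target)², gives nearly the same values: 152.4 s and 76.2 s. Either target alone could have produced 45: a round SD of 150 s with 90 s, or of 75 s with 45 s, each gives 45 per group by the t calculation. The two together could not.

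**3. Hold one SD and test the other target.**

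| SD | Target | Power at 45 per group | n per group for 80% |
|---|---|---|---|
| 150.7 s | 90 s | 80% | 45 |
| 150.7 s | 45 s | 29% | 178 |
| 75.4 s | 45 s | 80% | 45 |
| 75.4 s | 90 s | >99.9% | 13 |

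**4. Could one figure be an SD?**

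- SD 90 s, target 45 s: 64 per group (two-sample) or 34 (paired).
- SD 45 s, target 90 s: 2 × 7.85 × (45/90)² = 3.9, so about 4 per group by the normal approximation.

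Neither gives 45.

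**5. Other tests.** The implied SDs for 90 s and 45 s are 170.4 s and 85.2 s for a one-sided test, 210.8 s and 105.4 s for a paired test, and 136.5 s and 68.2 s at alpha 0.025. The 2:1 ratio remains in each case.

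**6. Mixed reading: 90 s between groups at a visit, 45 s within patient.** The first needs an SD of LT of 150.7 s. The second, a paired test on 45 patients (d = 0.427), needs an SD of change of 45 / 0.427 = 105.4 s. With equal variances at both times, SD(change)² = 2 × SD² × (1 − r), so

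r = 1 − 105.4² / (2 × 150.7²) = 1 − 11,109 / 45,421 ≈ 0.76.

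This is possible, but the primary endpoint is the change. With an SD of change of 105.4 s, a between-group difference of 90 s needs only 23 per group. With 45 per group, the difference detectable at 80% power is 0.597 × 105.4 ≈ 63 s, which is neither printed figure.

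If instead the SD of change is 150.7 s, so that 90 s between groups is right, the paired test for 45 s has about 50% power at 45 patients and needs 90.

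**The case against.** The best defence is that two analyses are planned, one between groups and one within patient, and that the sample size sentence itself says *difference* for 90 s and *change* for 45 s. On that reading the figures are not arithmetically incompatible. This stands as a possibility. However, the article does not state it, it depends on an unprinted correlation of about 0.76, and it leaves the between-group test on the primary endpoint without a target that matches 45 per group.

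A second defence is that a journal article condenses the full protocol, so the missing SD may be given there. This also stands, and the absence of an SD is not the point made here. It does not rescue the sentence, because no single SD reconciles the two targets under one test.

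A reader might go further and infer that an SD of 75 to 151 s contradicts the article's own LT figures, so that the trial is badly underpowered. The documents do not support that:

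- The LT figures are cut-offs and shares beyond a cut-off. The share at or above 2500 s ("detected in 14% patients on admission was strongly related to recurrent major cardiovascular events") comes from an earlier study of ST-elevation infarction, whereas this trial enrols all acute coronary syndromes.
- The Status quo section reports that "a total of 65 patients were screened and 25 patients were randomised". The ratio 25/65 = 38% is not the share above 2000 s, because patients who decline or cannot consent also count as screen failures (Inclusion and exclusion criteria).
- The result turns on these unknowns. Suppose that LT is normal, 14% lie at or above 2500 s, and the correlation between visits is 0.9 (all assumed for this trial). If 38% exceed 2000 s, SD = 500 / (1.080 − 0.293) ≈ 635 s, the SD of change is 635 × √0.2 ≈ 284 s, and power for 90 s is about 32%. If 60% or 70% exceed 2000 s, power is about 71% or 86%. Lower correlations give lower power.
- Using the other cited share instead (23% at or above 3000 s) with 38% above 2000 s gives an SD of about 2245 s rather than 635 s.

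Inputs that move the answer this much can prompt a check of the SD. They cannot show a contradiction.

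**Conclusion.** The concern holds in a limited form. The article attaches 80% power at 45 per group to both 90 s and 45 s without naming the comparison for either, and under one two-sample test both cannot be true. The implied SD is about 151 s or about 75 s. At the larger SD, power for 45 s is about 29%; at the smaller, 90 s would need about 13 per group. These results assume a two-sample t test at two-sided alpha 0.05 with a common SD. The 2:1 conflict itself does not depend on the choice of test, provided that one test and one SD serve both targets.

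It is not shown that 45 per group is too few, nor that the true SD exceeds 151 s. For scale only, an assumed SD of change of 200 s would give 56% power for 90 s and 18% for 45 s. That is a reason to check the SD, not evidence of its value.

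**What to change.** Keep 150 patients and restate the calculation:

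1. Give one target difference for the primary endpoint, change in LT to 4 weeks. Name the between-group contrasts it applies to: Group 2 versus Group 1 and Group 2 versus Group 3, as in Statistical considerations.
2. State the SD used and its source, and say whether it is an SD of change or a residual SD after baseline adjustment.
3. Delete the other figure, or assign it to its own named test with its own SD.
4. Check the SD against the pooled SD of change, computed without arm labels, in patients already followed to 4 weeks. Ignoring the arms inflates it only slightly: at SD 151 s, a 90 s effect confined to one of three equal arms adds 90² × (1/3) × (2/3) = 1,800 to a variance of 22,801, giving about 157 s.
5. Restate either the power for the chosen target or the difference detectable with 45 per group, which is 0.597 × SD for each contrast at two-sided alpha 0.05.

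The cost is a change of wording and a short calculation, with no extra patients. The stated power may become less favourable.
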